### Interim analyses

We will carry out two interim analyses after trial completion of 25% and 50% of the planned number of included patients, separately for the two age groups. We will use the O’Brien-Fleming rule [37] for determining appropriate significance levels for each analysis, which is determined by time of hypothesis testing (*n*=3) and the overall significance level of *α*=0.05. Under these assumptions, the significance levels are 0.0006 for the first interim analysis, 0.0151 for the second interim analysis, and 0.0471 for the final analysis. Interim analyses will be carried out for both the primary endpoint (DASH) and for serious complications (iatrogenic nerve injury, deep infection, major adverse cardiac events (MACE), other major adverse events, and death) and will be conducted by one-sided tests to determine if the improvement in DASH is significantly above 25 points, respectively if the complication rate is at least 20% higher.

A Data Monitoring Committee (DMC) has been organized to monitor and evaluate the data from the interim analyses. The DMC consists of five independent members including the patient representative (PR), two orthopedic researchers, an orthopedic surgeon, and a nurse.

In the event of one group having zero complications, the significance level cannot be computed by a cChi-square test, and the DMC will have to assess the data due to a statistical variation.

In the event of a patient sustaining several complications, the most severe complication will follow the patient. The complications are ranked in a hierarchy model describing the severity and are ranked from most severe to least severe: death, MACE, deep infection with debridement, other reasons for hospitalization, and iatrogenic nerve injury.

The interim analyses will be conducted by a biostatistician, blinded to the treatment allocation. Data will then be presented to the DMC, in means and proportions and be accompanied with confidence intervals. The DMC will have access to the data unblinded, and if at least one of those two conditions is fulfilled or a statistical variation has occurred at an interim analysis the DMC will be asked to investigate the results in detail and present their recommendation to continue or stop the trial. In the event of disagreement with a split decision (one or more casts a blank vote), the steering committee will be involved in discussing the stopping of the trial.

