Furthermore, the steering committee will be monitoring recruitment and drop-out. Any modification in design and recruitment will be registered on ClinicalTrials.gov.

If it is observed that inclusion of patients in the two age groups is too slow, it can be decided to pool the age groups and analyze them as one total group instead. If this decision is made before the first interim analysis, the above significance levels will be used for the total group. If the decision is made between the first and second interim analysis, O’Brien-Fleming significance levels for four analyses will be used, resulting in a significance level of 0.0184 for the second interim analysis and 0.0412 for the final analysis. If the decision is made after the second interim analysis, the O’Brien-Fleming significance level for five analyses will be used, resulting in a significance level of 0.0417 for the final analysis.

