## Statistical analysis plan

### Hypothesis

The null hypothesis is:The DASH score at 52 weeks after surgical treatment is not superior to non-surgical treatment with the option of early crossover surgery in patients with humeral shaft fractures

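### The interim DASH tests use a 25-point null while the final test uses plain superiority, and the O'Brien-Fleming levels do not match looks at 25% and 50%; the 5% error rate still holds as written.

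*Protocol article*

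**What the plan says.** Interim analyses are planned, separately by age group, "after trial completion of 25% and 50% of the planned number of included patients". The O'Brien-Fleming levels rest on "time of hypothesis testing (*n*=3) and the overall significance level of *α*=0.05", and "the significance levels are 0.0006 for the first interim analysis, 0.0151 for the second interim analysis, and 0.0471 for the final analysis". The interim DASH comparisons are "one-sided tests to determine if the improvement in DASH is significantly above 25 points". Meeting this condition, or the separate complication condition, leads the DMC to examine the data and recommend whether to continue.

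The Hypothesis section sets a different null for the final comparison: "The DASH score at 52 weeks after surgical treatment is not superior to non-surgical treatment", with no 25-point margin. Primary analysis applies 0.0471 to that comparison. Sample size powers the trial for 7 points (SHAFT-Y) and 10 points (SHAFT-E).

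If the age groups are pooled between the first and second interim analyses, the plan uses levels for four analyses, "resulting in a significance level of 0.0184 for the second interim analysis and 0.0412 for the final analysis". If they are pooled after the second, it uses levels for five, "resulting in a significance level of 0.0417 for the final analysis".

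**The concern.** An O'Brien-Fleming correction shares one error rate among repeated tests of the same null at known information fractions. Neither condition is met here. The interim null is a difference of at most 25 points, which is 25/7 = 3.6 times the planned effect in SHAFT-Y and 25/10 = 2.5 times in SHAFT-E, and the protocol does not explain it. The levels also depend on when the looks occur, but the protocol derives them from the number of tests alone.

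At stake are the thresholds that decide the primary endpoint. The final test is tightened to pay for looks that cost nothing. The two defects also mask each other: someone who later corrects the interim null to zero but keeps the levels would break the 5% error rate. If the groups are pooled, the primary result would be judged against levels that do not agree with one another.

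**Working it through.** **Inputs.** From Sample size: SD 14.91 and 18.59, effects 7 and 10, N = 163 and 124, alpha 0.05, power 0.80, attrition 15%. From Randomization: 1:1 allocation. From Interim analyses: looks at 25% and 50%, and the stated levels.

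**1. Sample size and sidedness.** n per arm = 2(1.960 + 0.842)² SD²/difference² = 71.2 and 54.3. Rounded down, doubled and multiplied by 1.15, this gives 142 × 1.15 = 163 and 108 × 1.15 = 124, as stated. With one-sided 0.05 (1.645 in place of 1.960) n would be 56.1 and 42.7 per arm, which does not lead to 163 and 124. So the final test appears to be two-sided, though the protocol does not say so.

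**2. Difference needed to trigger the efficacy look.** Threshold = 25 + z(1 − level) × SD × √(2/n per arm), with one-sided z = 3.239 for 0.0006 and 2.167 for 0.0151.

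| Group, look | n per arm | SE | Threshold | Probability at planned effect |
|---|---|---|---|---|
| SHAFT-Y, 25% | 20.4 | 4.67 | 40.1 | 7e-13 |
| SHAFT-Y, 50% | 40.8 | 3.30 | 32.2 | 1e-14 |
| SHAFT-E, 25% | 15.5 | 6.68 | 46.6 | 2e-8 |
| SHAFT-E, 50% | 31.0 | 4.72 | 35.2 | 5e-8 |

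With 15% attrition the thresholds are 41.4, 32.8, 48.5 and 36.1, and every probability stays below 2e-7. At twice the planned effect the probability is at most 8e-8 (SHAFT-Y) and 8e-4 (SHAFT-E). At a true difference of 35 points the second look triggers with probability 0.81 (SHAFT-Y) and 0.48 (SHAFT-E), using full planned numbers.

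**3. Error rate and power as written.** Under zero difference the interim tests cross with probability below 1e-11, so overall type I error equals the final level, about 0.0471. The critical value moves from 1.960 to 1.985. At the planned effect, power becomes Φ(2.802 − 1.985) = Φ(0.816) = 79.3%, against 80.0%.

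**4. Do the levels fit the schedule?** An O'Brien-Fleming boundary keeps z√t constant. The stated levels, read as two-sided, give z = 3.432, 2.430 and 1.985.

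| Information fractions | z√t |
|---|---|
| 1/3, 2/3, 1 | 1.981, 1.984, 1.985 |
| 0.25, 0.50, 1 | 1.716, 1.718, 1.985 |

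The levels therefore have the equal-thirds shape. Solving for overall two-sided 0.05 by numerical integration gives:
- equal thirds: constant 2.004, levels 0.0005, 0.0141, 0.0451. The stated figures are near these but do not match, and their total at equal thirds is 0.0524.
- 25/50/100%: constant 1.978, levels 0.00008, 0.0052, 0.0480. The stated interim levels are about 7 and 3 times larger.

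Applied to a zero null at 25/50/100%, the stated levels give a total of 0.0552 two-sided (0.0540 if all tests are one-sided).

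**5. Pooled levels.** For the four-analysis levels, 2.357 × √0.75 = 2.042 and 2.042 × √1 = 2.042. So 0.0184 is on the same boundary as 0.0412 only if the second interim sits at 75% information, the third of four equally spaced looks. Exact equal-spacing values are:

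| Level | Stated | Equal spacing |
|---|---|---|
| Third of four | 0.0184 | 0.0194 |
| Fourth of four | 0.0412 | 0.0429 |
| Fifth of five | 0.0417 | 0.0413 |

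On equal spacing the final level falls as looks are added (0.0451, 0.0429, 0.0413 for three, four and five). The stated pair rises.

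**The case against.** The strongest reply is that nothing here harms the trial's conclusion. Requiring a difference significantly above 25 points is stricter than testing against zero, a very high bar for early efficacy can be a legitimate choice, and crossing it leads to DMC review and not to an automatic stop. The one threshold that decides the result, 0.0471, is conservative and only 0.0009 below the 0.0480 that fits the schedule. All of this stands, and it sets the weight of the point.

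It also rules out three stronger readings that a reader might infer:
- That the efficacy look can never trigger. It can, at true differences well above 25 points, and the complication trigger is separate.
- That type I error is inflated. The 0.055 arises only if the interim null is changed to zero and the stated levels are kept; the protocol does not do that.
- That every stated level is materially wrong. None of the levels reproduces to four decimals, but the material mismatch is in the two interim levels, which have almost no effect under a 25-point null.

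It is also fair that the correct pooled levels cannot be derived from this document, because it gives no information fractions for pooled looks. The equal-spacing values show only that the stated levels disagree with each other on the count-based approach the protocol follows.

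The reply does not explain the 25 points, why alpha is given up for looks that spend none, or why the final level should rise with an extra analysis.

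**Conclusion.** The inconsistency holds in three parts: different nulls at the interim and final tests, levels shaped for equally spaced looks instead of 25% and 50%, and pooled final levels in the wrong order. The cost as written is small: overall error of about 0.047 in place of 0.05, and about 0.7 percentage points of power. The point is worth correcting before interim data are seen, but it is below the level of an essential change because the error rate is protected.

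Assumptions: improvement in DASH means the between-group difference; SDs are as planned; the normal approximation applies, with information proportional to patients analysed; the final test is two-sided. If the final test were one-sided at 0.05, the O'Brien-Fleming levels at 25/50/100% would be 0.0004, 0.0088 and 0.0466, so the replacement figures depend on sidedness, but the mismatch does not.

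**What to change.** Correct the null and the levels together, in one of two ways.

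(a) Declare the 25-point look a non-binding guideline for the DMC that spends no alpha, and test each age group's final comparison at two-sided 0.05 in place of 0.0471.

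(b) Test zero difference at every look, with O'Brien-Fleming boundaries computed at the actual information fractions: two-sided, about 0.00008, 0.0052 and 0.0480 at 25/50/100%.

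Under either option, state the sidedness of the final test. Replace 0.0184, 0.0412 and 0.0417 with levels computed from the actual information fractions of the pooled looks. Do not simply drop all adjustment when pooling is decided after interim looks: the DMC sees unblinded data, and the patient representative sits on both the DMC and the steering committee, which can decide to pool.

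The complication test uses the same interim levels, so say explicitly which levels apply to it after the change.

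Cost: wording in Interim analyses, Sample size and Primary analysis, plus a short boundary calculation. No extra patients or data are needed. Option (a) makes the final test slightly less strict than 0.0471; option (b) does so by 0.0009.

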### Randomization

A computerized database software, Research Electronic Data Capture (REDCap)© [38] will be used to generate an irreversible random allocation sequence and perform block randomization with selected block sizes of 2 and 4, which will be stratified on site and age (18–64 and +65). Patients will be assigned to the trial with an allocation of 1:1 to either surgical treatment or non-surgical treatment. The trial worker acquires the allocated treatment from the central coordinator with randomization rights to REDCap. The trial worker then initiates the treatment, either by scheduling the surgery date or applying the chosen non-surgical method.

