### Sample size

The two groups (SHAFT-Y and SHAFT-E) require individual sample size calculations. Two standard deviations (SDs) were obtained from the data of the FISH trial [13] and were separated in age groups of 18–64 years and 65 years and above. By the distribution-based approach, one half a SD corresponds to the minimal important change (MIC) [49]. The calculations are powered to detect a MIC of 7 points in the young and 10 points in the elderly group in DASH, respectively. Two independent means sample size calculations were performed. For SHAFT-Y the following data were included: mean difference = 7.0, SD= 14.91, *α*= 0.05, and power= 0.8. For SHAFT-E the following data were included: mean difference= 10.0, SD= 18.59, α= 0.05 and power= 0.8. Based on the preceding assumptions and including an attrition of 15%, the total sample size is estimated to 163 patients for SHAFT-Y and 124 patients for SHAFT-E.

The FISH trial [13] experienced 5% attrition, since more sites are involved in SHAFT the attrition is set to 15%.

The steering committee can decide to pool data from both RCTs (SHAFT-Y, SHAFT-E) if recruitment is prolonged.

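### The interim trigger for serious complications rests on a false zero-count rule, a test that does not match its 20% hypothesis, and an efficacy significance level applied to harm

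*Protocol article*

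**What the plan says.** The Interim analyses section of the protocol article plans looks at 25% and 50% of the planned patients, separately in each age group. The levels are 0.0006 and 0.0151, derived by the O'Brien-Fleming rule for three analyses at an overall 0.05. These levels serve both the primary outcome (DASH) and a composite of serious complications. For complications the one-sided question is "respectively if the complication rate is at least 20% higher".

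The section then states: "In the event of one group having zero complications, the significance level cannot be computed by a cChi-square test". It calls that case a statistical variation and hands it to the DMC.

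The DMC is asked for a detailed investigation and a recommendation to continue or stop "if at least one of those two conditions is fulfilled or a statistical variation has occurred". The same section says that interim results are presented to the DMC as means and proportions with confidence intervals, and that the DMC has unblinded access.

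**The concern.** Three things in the complication rule do not fit together.

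1. The reason given for the zero-count clause is not true of a chi-square test. The clause nevertheless makes a difference of a single event a formal trigger.
2. A chi-square tests zero difference. The hypothesis is an excess of at least 20%, and the text does not say whether that means percentage points or a ratio. The biostatistician cannot apply the rule as written without choosing a test.
3. O'Brien-Fleming levels are strict early in order to prevent premature claims of benefit. Applied to harm, the same strictness makes the formal alarm hardest to set off at the first look.

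At stake is when the DMC is formally asked to investigate nerve injury, deep infection, cardiac events, other major events or death. The type I error of the DASH comparison is not involved.

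**Working it through.** **Interim sizes.** The Sample size section gives "mean difference = 7.0, SD= 14.91" for SHAFT-Y and "mean difference= 10.0, SD= 18.59, α= 0.05 and power= 0.8" for SHAFT-E. The formula n per arm = 2(SD/difference)²(1.960 + 0.842)² gives 71.2 and 54.2. Doubling and multiplying by 1.15 for attrition gives 163.8 and 124.8, which agrees with the stated 163 and 124. With 1:1 allocation:
- SHAFT-Y: 163 × 0.25 / 2 ≈ 20 per arm at the first look, and 163 × 0.50 / 2 ≈ 41 at the second.
- SHAFT-E: 124 × 0.25 / 2 = 15.5 (15 or 16) per arm, and 124 × 0.50 / 2 = 31.

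**Zero counts.** For a 2×2 table, chi-square = N(ad − bc)² / (product of the four margins).
- 0/20 vs 1/20: 40 × 20² / (20 × 20 × 1 × 39) = 1.03, p = 0.31.
- 0/20 vs 6/20: 40 × 120² / (20 × 20 × 6 × 34) = 7.06, p = 0.008.

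The statistic fails only when both groups have no events.

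**What the first look needs (SHAFT-Y, 20 per arm, one-sided 0.0006, critical z = 3.239).**
- Wald test with a 20-point margin, z = (p1 − p2 − 0.20)/√[p1(1 − p1)/n + p2(1 − p2)/n]. For 13/20 vs 1/20: 0.40/0.1173 = 3.41, fires. For 12/20 vs 1/20: 0.35/0.1199 = 2.92, does not.
- Plain chi-square of zero difference (pooled z). For 11/20 vs 1/20: 0.50/0.1449 = 3.45, fires. For 10/20 vs 1/20: 0.45/0.1412 = 3.19, does not.
- Other readings against 1/20: a linear contrast for a relative 20% needs 10/20, Fisher's test 12/20 and a score test with the 20-point margin 15/20. A log risk ratio test against 1.2 cannot fire.
- 9/20 vs 1/20 misses on each: margin z = 1.65; chi-square one-sided p = 0.0017; Fisher p = 0.004.

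**How often each route fires.** Complication rates are not in the document, so the rates below are assumptions. With equal rate p and q = (1 − p)ⁿ, the chance of exactly one empty group is 2q(1 − q). At 5% and n = 20, q = 0.3585, so 2 × 0.3585 × 0.6415 = 0.46.

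| Equal true rate | SHAFT-Y look 1 (20 per arm) | SHAFT-E look 1 (15 per arm) |
|---|---|---|
| 5% | 46% | 50% |
| 10% | 21% | 33% |
| 15% | 7.5% | 16% |
| 20% | 2% | 7% |

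Under harm at the SHAFT-Y first look, exact binomial enumeration gives, for either route:
- 30% vs 5%: the zero-count clause fires in 35.9%. The complication condition adds 0.05 percentage points (Wald margin) or 0.75 (chi-square), in total about 36% to 37%. With no harm at 5% the figure is 46%.
- 40% vs 10%: 13% (Wald margin) or 17% (chi-square), against 21% with no harm at 10%.

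**Second look (SHAFT-Y, 41 per arm, one-sided 0.0151, critical z = 2.167).** Here the reading decides.
- Wald margin: needs 18/41 vs 2/41. At 35% vs 5% it fires in about 12% outside zero counts, or 24% with the zero-count route.
- Plain chi-square: needs 9/41 vs 2/41. At 35% vs 5% it fires in about 93%.

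**The case against.** A reader might infer that the DMC is summoned by chance and kept from harm, or that the alarm is dead at both looks. The document does not support either reading.

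- **Access to data.** The DMC receives proportions with confidence intervals and has unblinded access at every look. Nothing forbids it from raising 9/20 vs 1/20 itself. The triggers add a formal request; the text does not say that review happens only then.
- **Second look.** The test the protocol names is a chi-square. On that reading the second look is nearly as sensitive as a Fisher test at one-sided 0.05 (93% against 96% at 35% vs 5%). Failure at the second look follows only from the margin reading.
- **Zero counts.** The clause also fires on none against many, where review is apt. Counting 0 vs 0 as well would raise the 46% to 59%, but in that case the chi-square really is undefined and the protocol is right.
- **Assumed rates.** The composite includes all-cause hospitalization, so rates may be well above 5%. At 15% to 20% in both arms the clause seldom fires in SHAFT-Y.

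All four points stand and limit the finding. None of them rescues the false statement about the chi-square, the mismatch between test and hypothesis, or the use of 0.0006 for harm at the first look.

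**Conclusion.** The formal complication trigger is wrong as written and should be fixed. Two defects need no assumption about event rates: the chi-square is computable with one empty group, and it does not test an excess of 20%, which is itself undefined. The third holds under every test reading examined: at the first SHAFT-Y look the condition needs at least 10/20, and 11/20 to 13/20 on the two most natural readings, against 1/20.

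The reversal at that look, with review less likely at 30% vs 5% (about 36%) than at 5% in both arms (46%), depends on low assumed rates. At the second look the size of the problem depends on which test is meant. What is affected is the formal request for detailed review and a recommendation to continue or stop. The DMC's access to data and the DASH type I error are not affected.

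**What to change.** Rewrite the complication part of the paragraph, and match it in the DMC charter:
- Delete the zero-count clause and the 20% margin.
- At each look compare the proportion with a serious complication against zero difference, using a test valid for small counts such as Fisher's exact test.
- Use a fixed review level that is not taken from the efficacy boundary, for example one-sided 0.05, and state which arm's excess is tested.
- State that the DMC may review the safety data and make a recommendation whether or not the trigger is met.

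At an assumed 35% vs 5%, Fisher's test at one-sided 0.05 triggers in about 69% and 96% of SHAFT-Y looks 1 and 2, and in 53–56% and 88% in SHAFT-E. False triggers are about 2.5% or fewer at equal rates of 5% to 15%; testing for an excess in either arm would double that to about 5%.

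The cost is one paragraph, with no change to sample size or DASH alpha. The DMC would make somewhat more detailed reviews when a real imbalance exists. The gain is not uniform: at the first SHAFT-E look with 30% vs 5%, Fisher triggers in 38–43%, slightly below the present combined rule (44–47%, mostly through the zero-count clause). The exact level is therefore a choice for the charter, and the statement that the DMC may act without a trigger matters.

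### Pooling the age groups for slow recruitment also pools the interim complication test, so the age-specific safety trigger is lost at every interim still to come

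*Protocol article*

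**What the plan says.** All of this is in the protocol article, section Interim analyses, unless noted.

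- The interims are run "after trial completion of 25% and 50% of the planned number of included patients, separately for the two age groups".
- They cover two endpoints: "Interim analyses will be carried out for both the primary endpoint (DASH) and for serious complications". The stated levels are 0.0006 and 0.0151 at the interims and 0.0471 at the end.
- The DMC is asked to investigate in detail and to recommend continuing or stopping "if at least one of those two conditions is fulfilled or a statistical variation has occurred at an interim analysis". The last condition refers to a group with no complications, where the chi-square test cannot be computed.
- If inclusion is too slow, "it can be decided to pool the age groups and analyze them as one total group instead".
- The levels then follow the timing. "If this decision is made before the first interim analysis, the above significance levels will be used for the total group". For a decision between the two interims, four analyses are counted, "resulting in a significance level of 0.0184 for the second interim analysis and 0.0412 for the final analysis". For a decision after the second interim, only a final level is given (0.0417).
- The section Sample size repeats that the steering committee may pool if recruitment is prolonged. It exempts no endpoint either.
- The section Randomization says that allocation is by blocks "which will be stratified on site and age".

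**The concern.** The complication test is one of the interim analyses, those analyses are by age group, and pooling puts a total-group analysis in their place. Read as written, a decision taken for recruitment reasons also switches off the safety trigger by age.

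The reason for pooling does not carry over. Slow recruitment limits power for DASH, which is an argument for combining the groups on DASH. It is no argument for ceasing to ask whether one treatment harms the elderly in particular. The protocol treats the two groups as different: separate sample sizes, separate crossover windows and independent analysis.

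The trigger counts death, major adverse cardiac events and hospitalisation, together with deep infection and iatrogenic nerve injury. If the first three fall mostly on patients aged 65 and over (an assumption; the article gives no event rates), an excess confined to that group is averaged with the young. The rule is then less likely to oblige the DMC to look.

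**Working it through.** **1. Which looks are affected.**

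| Pooling decided | Age-specific complication triggers lost |
|---|---|
| Before the first interim | both interims |
| Between the interims | the second interim |
| After the second interim | none |

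**2. Dilution.** Planned numbers are 163 and 124, total 287. The elderly share is 124/287 = 0.432. An excess confined to the elderly shrinks in the total group to 0.432 × 30 = 13.0 points, or 0.432 × 20 = 8.6 points.

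**3. Numbers per arm at each look (1:1).**
- 50% look: elderly 124/2/2 = 31; young 163/2/2 ≈ 41; total 72.
- 25% look: elderly 124/4/2 ≈ 15; young 163/4/2 ≈ 20; total 35.

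**4. Test.** With event proportions p₁ and p₂ in two arms of n and their average p̄, z = (p₂ − p₁)/√(p̄(1 − p̄)·2/n). It fires one-sided at level α if z > z(1 − α). The probability of firing is summed exactly over the binomial outcomes. All event rates are assumptions. The protocol's condition of a rate 20% higher does not say whether this is absolute or relative, so the main figures use a plain test of no difference.

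**5. Excess in the elderly only, 50% look.**

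| Elderly rates | Elderly alone, α 0.0151 | Pooled, α 0.0151 (young 2% / 5% / 10% in both arms) | Pooled, α 0.0184 (same young rates) |
|---|---|---|---|
| 10% v 40% | 76% | 62% / 55% / 47% | 66% / 60% / 51% |
| 10% v 30% | 44% | 34% / 29% / 24% | 36% / 32% / 27% |

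The more lenient 0.0184 recovers only part of the loss.

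**6. 25% look, α 0.0006, elderly 10% v 40%.** Elderly alone 6%; pooled 1–2%. The separate trigger is already weak here.

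**7. Zero-count rule, 50% look, elderly 10% v 40%, young 5% in both arms.** Chance that at least one arm has no event:
- elderly: 1 − (1 − 0.9³¹)(1 − 0.6³¹) = 3.8%
- young: 1 − (1 − 0.95⁴¹)² = 23%
- pooled: about 0.9³¹ × 0.95⁴¹ = 0.0381 × 0.122 = 0.5%

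**8. Harm common to both ages, 10% v 30%, α 0.0151.** Elderly alone 44%; young alone 55%; either of the two 1 − (1 − 0.443)(1 − 0.551) = 75%; pooled 82%. Here pooling helps.

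**9. All three tests together (simulation, 400,000 runs, α 0.0151).** Elderly-only excess: 77–78% for 10% v 40% and 47–48% for 10% v 30%. Common harm: 85%. No excess (elderly 10%, young 2–10%): 2.0–3.4%, against about 1.5% for the pooled test alone.

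**10. Other readings of 20% higher** (elderly 10% v 40%, young 5% in both arms, 50% look, α 0.0151). Relative margin: 67% elderly alone, 42% pooled. Absolute margin: 13% elderly alone, about 0% pooled. The direction is the same.

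**The case against.** **The text is silent, and this is an article.** The pooling paragraph is about resetting O'Brien-Fleming levels and does not mention complications. How a DMC tabulates safety after a design change is often settled elsewhere. But the article itself defines the interim analyses as covering both endpoints, says that the total group replaces the age groups, and fixes timing and levels. That is a stated rule, not a detail left open.

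**The DMC can look anyway.** It receives means and proportions with confidence intervals, has unblinded access, and the trigger is advisory. This stands, and it limits the point: the formal prompt is lost, not all monitoring by age.

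**No excess in the young is the least favourable case for pooling.** Infection and iatrogenic nerve injury are in the composite and are not confined to the elderly. At the 50% look (α 0.0151), with young rates of 5% v 10%, pooled against elderly alone is 71% v 76% (elderly 10% v 40%) or 46% v 44% (10% v 30%). With young 5% v 15% it is 83% v 76% or 63% v 44%. These figures are right. They argue for having the total-group test, not for dropping the others, and running all three is never less sensitive than any one of them.

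**The simulated test may not be the protocol's.** This is fair. On the absolute reading even the age-specific trigger would seldom fire, so the percentages are illustrations. The direction holds on each reading tried.

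**It is doubly contingent.** Harm requires pooling before the second interim and an excess largely confined to one age group. This stands: because the first look is weak, the practical loss is mainly at one look.

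**Conclusion.** The concern holds. As written, pooling for slow recruitment replaces the age-specific complication test and zero-count rule with total-group versions at every interim that remains: two, one or none, depending on timing.

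With an excess confined to the elderly, the chance that the second-look test obliges a DMC review falls from 76% to 47–62% (10% v 40%) or from 44% to 24–34% (10% v 30%) at 0.0151, and somewhat less at 0.0184. These sizes rest on assumed event rates, the planned age mix, no excess in the young and a plain test of no difference. They shrink or reverse as harm becomes common to both ages. The loss is of an obligation to review. It should be corrected before any pooling decision, because the repair is cheap and concerns patient safety.

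**What to change.** Add one sentence to the pooling paragraph of Interim analyses: pooling replaces the separate analyses for DASH only; at each remaining interim the complication trigger, including the zero-count rule, is applied within 18–64, within 65 and over, and to the total group, at the level already stated for that look. Show the DMC the complication tables by age group.

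The cost is that sentence and a table split by an existing stratification factor. With no excess in either group, referrals from the tests at the 50% look (0.0151) rise from about 1.5% to 2.0–3.4%. The zero-count rule kept by age adds more when events are rare (23% of looks in the young at 5% in both arms), as it would if the groups were never pooled. All of these are advisory reviews, not automatic stops. The DASH significance levels are unaffected.
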